**Fig. 2 Fig2:**
[figure not shown]
Map of study clusters in the three intervention districts

The selection of study clusters provides variation in the social franchise that facilitates identification of its impact. Variation over time is generated in two ways. The 2-year recall period of the household survey means that we have almost 12 months of baseline data even in areas where social franchising is introduced. Moreover, we anticipate that over time, some of the Group B study clusters will become intervention areas as the social franchise network expands generating further variation over time. Geographical variation in the placement of the social franchise is generated by our selection of comparison areas.

### Data collection

The evaluation relies primarily on several tools that are administered over two rounds of data collection: a household survey of women who recently gave birth and a health provider survey. The first round of data collection was in January 2015, and the second round is planned for March 2016. This means the impact of the social franchise intervention is assessed approximately 2 years after its start. Information on the precise timing of the introduction of social franchising in each cluster is based on administrative data provided by the franchisor triangulated with responses to the health provider survey. It is worth noting that the research outlined in this protocol is closely coordinated with several other data collection activities—direct observations of births and a case study of three social franchise models that will provide additional insights.

The household survey is administered to women as a cross-section at two points in time and serves as the main source of data on our study outcomes. Eligible respondents include all women who gave birth in the previous 24 months (first round) or 18 months (second round), including those who had a stillbirth or whose child died since birth. Eligible women are identified through a census of households, conducted 1 month before the household survey. Every member of the household is listed and then, for women aged 15 to 49 years, a series of questions probe whether she gave birth to a baby that was born alive, born dead or lost before birth. Using this sampling frame, a maximum of 23 eligible women in each cluster are randomly selected for interview. The household survey tool includes the following modules: (1) household listing, (2) general healthcare interactions, (3) household characteristics, (4) wellbeing of husband, (5) pregnancy history, (6) family planning and antenatal care, (7) delivery and postnatal care, (8) child health, (9) interactions with community health workers, (10) information and perceptions of healthcare, and (11) wellbeing, mental health and physical health.

The health provider survey is administered at the same time as the household survey within the same communities. The sampling frame is generated from a census of all health providers within the study clusters conducted 1 month prior to the health provider survey. The census records the type of health provider and its geographic coordinates. For the purposes of the census, we define a health provider as any institution or individual whose primary purpose is to provide healthcare. We exclude drug sellers. Using this list, we randomly select for interview one private health provider (social franchisee in intervention clusters), one government health provider and one accredited social health activist in each cluster. The health provider survey tool includes the following modules: (1) health facility characteristics, (2) key health worker characteristics, (3) reproductive, maternal and newborn services, (4) maternal health knowledge, (5) maternal health practice, (6) motivation, (7) social franchise and business practices, and (8) experience of social franchise network.

### Outcomes

The impact of the social franchise model is assessed using a comprehensive set of pre-specified outcomes that are measured using the household data. An extensive list of outcomes, 59 indicators in total, is shown in Tables 2, 3 and 4. They cover the continuum of care from antenatal care through postnatal family planning and include various types of indicators including healthcare utilisation, process of care, healthy behaviour, patient experience, patient information and financial strain. The study outcomes are organised according to conceptually similar groups that are required when implementing methods to deal with many outcomes.

**Table 2 Tab2:** Antenatal outcomes of the impact evaluation by domain

Indicator	Type of indicator
1. ANC utilisation	
Received at least three ANC visits (%)	Use of healthcare
Received ANC visit in first trimester (%)	Use of healthcare
Number of ANC consultations (visits)	Use of healthcare
Received visit from ASHA during pregnancy (%)	Use of healthcare
2. ANC content of care	
Fully immunised with tetanus toxoid (%)	Process of care
Received iron supplementation during pregnancy (%)	Process of care
Took iron supplementation during pregnancy for at least 100 days (%)	Process of care
Received test results for syphilis received (%)	Process of care
Abdominal examination during ANC (%)	Process of care
Received a drug for intestinal worms during pregnancy (%)	Process of care
Received a drug to prevent malaria (%)	Process of care
Multiple birth pregnancy detected during ANC (%)	Process of care
ANC content of care score of six items (index 0 to 1)	Process of care
3. ANC knowledge and preparedness	
Mother knowledge of pregnancy complications (index 0 to 1)	Patient knowledge
Mother knowledge of signs of delivery complications (index 0 to 1)	Patient knowledge
Birth preparedness (financial, transport, blood donor, attendant, safe delivery kit) (index 0 to 1)	Healthy behaviour

**Table 3 Tab3:** Intrapartum care outcomes of the impact evaluation by domain

Indicator	Type of indicator
1. Delivery care utilisation	
Gave birth in a health facility (%)	Use of healthcare
Gave birth with a doctor, nurse or midwife (%)	Use of healthcare
Had a caesarean section (%)	Use of healthcare
2. Recommended delivery care practices	
Delivery attendant used gloves (%)	Process of care
Delivery attendant washed hands with soap (%)	Process of care
Woman had her BP measured (%)	Process of care
Mobility during labour (%)	Process of care
Oral fluids during labour (%)	Process of care
Heart rate of baby monitored with intermittent or continuous auscultation (%)	Process of care
Use of anti-shock garment (%)	Process of care
3. Harmful or ineffective delivery care practices	
Shaving pubic hair (%)	Process of care
Enema given (%)	Process of care
Lithotomy position during labour (%)	Process of care
Intravenous fluids during labour (%)	Process of care
4. Delivery care practices frequently over used	
Urinary catheter (%)	Process of care
Pain control by epidural analgesia (%)	Process of care
Oxytocin augmentation (%)	Process of care
Episiotomy (%)	Process of care
5. Disrespect and abuse	
Support during labour (%)	Patient experience
Medical procedure performed without consent (%)	Patient experience
Shouted, scolded or humiliated by health worker (%)	Patient experience
Slapped, pinched or hit by health worker (%)	Patient experience
Gave birth with privacy (%)	Patient experience
Refused care for inability to pay (%)	Patient experience
Kept in facility for inability to pay (%)	Patient experience
Felt disrespected or abused during facility stay (%)	Patient experience
6. Economic consequences	
Out-of-pocket spending on delivery care (NRS)	Financial strain
Borrowed money to pay for delivery care (%)	Financial strain
Household in debt to pay for delivery care (%)	Financial strain
Received JSY cash incentive (%)	Financial strain

**Table 4 Tab4:** Postpartum and newborn outcomes of the impact evaluation by domain

Indicator	Type of indicator
1. Postpartum care	
Received postpartum care within 48 h of birth (%)	Use of healthcare
Newborn received postnatal care within 48 h of birth (%)	Use of healthcare
2. Newborn content of care	
Clean cord care (clean instrument to cut and tie the cord, and nothing put on cord) (%)	Process of care
Thermal care (immediate drying, wrapping, skin to skin and delayed bathing) (%)	Process of care
Baby weighed at birth (%)	Process of care
Baby registered and received certificate (%)	Process of care
3. Neonatal health	
Neonatal mortality (per 1000 live births)	Health outcome
One-day mortality (per 1000 live births)	Health outcome
Birth weight (kg)	Health outcome
4. Breastfeeding	
Immediate breastfeeding within 1 h of birth (%)	Healthy behaviour
Colostrum given to baby (%)	Healthy behaviour
Exclusive breastfeeding for 3 days (%)	Healthy behaviour
5. Family planning	
Modern contraceptive use at 3 months postpartum (%)	Use of healthcare

In contrast to standard surveys on maternal and child health in India [28, 29], we seek to measure a range of intrapartum care practices that may be affected by the social franchise, given its focus on standards. We get at the issue of quality of care by collecting information on recommended delivery care practices, harmful or ineffective practices, frequently over-used practices and disrespect and abuse indicators [30–33]. The study will also collect data on a large range of characteristics of the mother and her household. These data are used to control for potential confounding and increase efficiency of our estimates. They are also important in examining the equity impact of the project—to see which socioeconomic segments of the population benefits most from the social franchise.

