### Sample size calculations

Household sample size calculations are based on an endline comparison of two groups (intervention versus control), using the proportion of women giving birth in a health facility as the primary outcome. On the basis of an observed institutional delivery rate of 50 % at baseline [10] and an assumed coefficient of variation of 0.2, a sample size of 60 intervention and 60 control clusters with a total of 20 women in each cluster are estimated to provide 80 % power to detect an 8 percentage point increase in the rate of institutional deliveries in the intervention group compared with the control at 5 % level of significance. Assuming a coefficient of variation of 0.1 reduces the detectable difference to 6 percentage points. It is anticipated that the study will have power to detect smaller differences once the analysis controls for covariates and utilises data from two survey rounds.

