The presence of multiple outcomes leads to the risk of arbitrarily selecting statistically significant outcomes where high values of test statistics arise by chance. Testing each hypothesis one at a time with a fixed significance increases the probability of a type-I error exponentially as the number of outcomes tested grows. We deal with multiple outcomes using several procedures that are implemented for conceptually similar groups of outcomes listed in Tables 2, 3 and 4 [35, 36]. First, we present standardised treatment effects by creating an index for multiple outcomes within each domain and testing for an effect on the index. Implicitly, this weighs each outcome the same within a domain. Second, we present family-wise *p* values adjusted to account for the multiple outcomes within a domain using the free step-down resampling method of Westfall and Young [37].

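### Caesarean section has no agreed favourable direction, yet it forms one third of the delivery care utilisation index and shares the multiplicity family of facility birth, the sample-size outcome

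*Protocol article*

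**What the plan says.** In the Outcomes section, Table 3, the first domain (delivery care utilisation) has three members: birth in a health facility, birth with a doctor, nurse or midwife, and "Had a caesarean section". All three are typed as use of healthcare.

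The Empirical analysis section gives two domain-level procedures. The first is a standardised index per domain, tested for an effect: "Implicitly, this weighs each outcome the same within a domain". The second is a set of family-wise p values within the domain, by Westfall-Young free step-down resampling. The same section also regresses each outcome on its own.

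The Sample size calculations section sizes the study "using the proportion of women giving birth in a health facility as the primary outcome", at an unadjusted 5% level. The article does not take that outcome out of its domain family.

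Table 3 also has a domain headed "4. Delivery care practices frequently over used", with urinary catheter, epidural, oxytocin augmentation and episiotomy. Caesarean section is not in it. In Table 4, family planning is a domain with a single outcome.

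**The concern.** A summary index can be read only if each component has an agreed good direction. Facility birth and skilled attendance have one. A population caesarean rate does not, because a rise can reflect met need, over-use or both. The protocol recognises over-use for other delivery interventions by giving them their own domain, but it places caesarean section beside facility birth.

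Two results are at stake. The domain 1 index could move because of caesareans alone and be taken for a change in access to delivery care. Standardising adds to this, because a rarer binary outcome has a smaller standard deviation and so counts for more per percentage point. Separately, a third family member raises the bar for the adjusted p value of facility birth, although the sample size made no allowance for multiplicity.

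**Working it through.** **1. The plan's own figure.** Inputs, all from Sample size calculations:

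- control proportion p0 = 0.50, from "observed institutional delivery rate of 50 % at baseline"
- target p1 = 0.58, from "80 % power to detect an 8 percentage point increase in the rate of institutional deliveries"
- women per cluster n = 20, with 60 clusters per arm
- between-cluster variation k = 0.2, from "an assumed coefficient of variation of 0.2"

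Sidedness is not stated; two-sided is used here.

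Unmatched cluster formula: c = 1 + (1.960 + 0.842)² × [p0(1−p0)/n + p1(1−p1)/n + k²(p0² + p1²)] / (p1 − p0)²

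- p0(1−p0)/n = 0.25/20 = 0.01250
- p1(1−p1)/n = 0.58 × 0.42/20 = 0.01218
- k²(p0² + p1²) = 0.04 × (0.25 + 0.3364) = 0.02346
- Sum = 0.04814
- c = 1 + 7.849 × 0.04814/0.0064 = 60.03 clusters per arm

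Power at 60 clusters is 79.98%, so the stated 80% for 8 points reproduces for facility birth tested alone. The non-centrality is 1.960 + 0.842 = 2.80.

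**2. Weight of caesarean section in the index.** With three equally weighted standardised components, a change of d in one of them shifts the index by (d/SD)/3, where SD = √(p(1−p)). Facility birth at 50% has SD 0.500. The caesarean rate is not in the article, so 5-15% is an assumption.

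| Assumed caesarean rate | SD | Points of facility birth matching 1 point of caesareans (0.500/SD) |
|---|---|---|
| 5% | 0.218 | 2.29 |
| 10% | 0.300 | 1.67 |
| 15% | 0.357 | 1.40 |

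At 10%, with caesarean section coded positive, a 3-point rise offsets a 5-point fall in facility birth (0.03/0.300 = 0.05/0.500 = 0.10), but only if skilled attendance does not move. If attendance also falls 5 points (SD 0.5 assumed), the offset needs 0.20 × 0.300 = 6 points. Coded negative, the caesarean shift has the same size and the opposite sign.

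**3. Power for facility birth within the family.** Assumptions: non-centrality 2.80 for facility birth; correlation of test statistics 0.6 or 0.8 between facility birth and attendance, and 0.25 of each with caesarean section. The free step-down procedure was simulated with multivariate normal statistics. The first-step 5% critical values are 2.36 and 2.33-2.34 for three outcomes, and 2.20 and 2.15-2.16 for two.

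| Which outcomes truly move (each at 2.80) | Power, three outcomes | Power, caesarean removed |
|---|---|---|
| Facility birth only | 67-68% | 73-74% |
| Facility birth and attendance | 70% | 77% |
| All three | 74-75% | 77% |

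If caesareans do not change, removing them recovers about 6-7 percentage points. If all three outcomes move, it recovers about 3, because rejecting caesarean section first eases the later steps. In every row power stays below 80% after removal; that remainder comes from sharing the family with attendance.

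**The case against.** **No sign is given.** A reader might infer that the protocol scores caesareans as a gain. It does not say so. The disrespect and abuse domain mixes favourable and adverse items, so signs must be set somewhere, possibly in Additional file 4, which is not shown. This stands: the positive sign is an inference from the utilisation label. It does not remove the problem, because either sign forces a direction on an outcome without an agreed one, and the grouping itself is fixed in the article.

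**The domain measures use, not benefit.** The programme aims to raise use of emergency as well as basic obstetric care, so caesarean section is a reasonable outcome. That justifies measuring it. It does not justify a third of an index whose other two members are read as progress.

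**A fall in facility birth would be hidden.** A reader might infer this too, but the documents do not support it. Each outcome has its own regression, so both facility birth and caesarean section are seen beside the index.

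**The power loss is partial and conditional.** This stands. Most or part of it, depending on which outcomes move, is due to attendance. The 80% base is a two-group endline calculation, whereas the planned difference-in-difference analysis uses covariates and both rounds and will have different power. The article also does not say that the conclusion on facility birth rests on the adjusted p value alone.

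**Conclusion.** The point holds for the index and for the adjusted p value, and not for the single-outcome estimate of facility birth. The index argument is the main one. It needs only the grouping and the equal weights, both in the article; its size (1.4-2.3 points of facility birth per point of caesareans) rests on the assumed 5-15% rate and 50% facility birth.

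The multiplicity argument is secondary. About 67-70% power with caesarean section against 73-77% without it depends on the assumed correlations, on no true effect on caesareans, and on the endline two-group calculation. The gain is smaller if caesareans also change. It would be wrong to blame caesarean section for the whole shortfall from 80%. Whether more caesareans would be good or bad in this population is a clinical question and is not judged here.

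**What to change.** Before round 2 data, move caesarean section out of the domain 1 index and Westfall-Young family into its own single-outcome domain, as Table 4 does for family planning. Report its estimate and confidence interval with a two-sided test and no pre-set favourable direction. Do not add a causal breakdown by public or private place of birth: the programme may change where women deliver, so those contrasts would condition on a consequence of the intervention.

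The change takes one line in Table 3 and one sentence of analysis text, and data collection is unaffected. Two costs remain. Caesarean section no longer contributes to a summary index. The regrouping also comes after round 1, which already includes births after franchising began, so its date and reason should be documented.

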## Methods

### Study setting

Uttar Pradesh is India’s fourth largest and most populous state with approximately 199.8 million people living in 18 divisions and 75 districts. If Uttar Pradesh were a country, it would be the fifth largest in the world in terms of population. The three districts in which the social franchising network is located have a population of 8.1 million and vary considerably in terms of demographic and health indicators (see Additional file 3). Kanpur Nagar is predominant urban, with higher literacy and lower mortality than the state average. By contrast, Kannauj and Kanpur Dehat are more typical of the state as a whole. Largely rural, they have poor literacy and high rates of maternal and child mortality that are comparable with the less developed countries in the world.

Across the continuum of care, large discrepancies in maternal and child health indicators are observed between the three districts [see Additional file 3]. For example, coverage of at least three visits of antenatal care in Kanpur Nagar is the highest at 51 % compared to 15 and 32 % in Kannauj and Kanpur Dehat, respectively. Despite government schemes to improve rates of institutional births, 54 % of deliveries occur at home in Uttar Pradesh (57 % in Kannauj, 40 % in Kanpur Nagar and 52 % in Kanpur Dehat). Of the home deliveries, 11 %, 53 % and 29 % were conducted by skilled health personnel in Kannauj, Kanpur Nagar and Kanpur Dehat, respectively.

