### Empirical analysis

The impact evaluation relies primarily on the household data. We use a difference-in-difference strategy to estimate impacts [34]. This involves a comparison of changes in the outcomes over time between the intervention and the comparison groups. The analysis exploits the longitudinal nature of the data generated by the recall period used in the two rounds of the household survey and information on the precise timing of the introduction of social franchising in each study area. Specifically, using individual level data, we regress each outcome on a dummy variable indicating whether social franchising has been introduced in the area at the time of birth, area fixed effects and quarter year fixed effects. Unadjusted estimates are reported as well as those that adjust for household characteristics. Controls for household characteristics include below the poverty line status, urban residence, religion, ethnicity, maternal education, parity, multiple birth and the recall period. We cluster the standard errors at the area level.

We test whether the social franchising model has an effect in two ways: the first analysis compares intervention areas with the two sets of comparison areas pooled together, and the second analysis compares the intervention areas with the comparison areas in adjoining districts without social franchising. The latter may arguably be less prone to selection bias since comparison areas in neighbouring districts are beyond the geographical reach of the project and may offer a more credible counterfactual. If the social franchising model is found to have an effect on any of the main outcomes, we conduct subgroup analyses with respect to below the poverty line status, maternal education and caste. Finally, to assess the so-called parallel trends assumption that underpins the difference-in-difference approach, we exploit the recall period in the household data to verify that trends in each of the outcomes are similar between the three study arms before the introduction of the social franchising model. Evidence of diverging pre-trends would be a cause for concern. Baseline outcomes and characteristics of women are also summarised for each study arm with continuous variables presented as mean (standard deviation) and categorical variables by frequencies (percentage). An additional file describes the empirical strategy of the impact evaluation in further detail [see Additional file 4].

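### Birth weight exists only for weighed babies, and weighing is itself a study outcome, so the birth-weight estimate and its third of the Neonatal health index are open to selection bias

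*Protocol article*

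**What the plan says.** In the Outcomes section, Table 4 puts "Baby weighed at birth" in domain 2 (Newborn content of care) as a process-of-care percentage. Domain 3 (Neonatal health) has three items: "Neonatal mortality (per 1000 live births"), one-day mortality, and "Birth weight (kg").

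The 59 indicators are described as a "comprehensive set of pre-specified outcomes that are measured using the household data". The Data collection section defines the survey population: "Eligible respondents include all women who gave birth in the previous 24 months (first round) or 18 months (second round"). No weighing of newborns by the study team is described. Study setting reports that "54 % of deliveries occur at home in Uttar Pradesh", with 57%, 40% and 52% in the three intervention districts.

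Under Empirical analysis the model reads "we regress each outcome on a dummy variable indicating whether social franchising has been introduced in the area at the time of birth", with area and quarter-year fixed effects and, in adjusted estimates, household and maternal characteristics and the recall period. Each domain is also combined into an index that is tested for an effect: "Implicitly, this weighs each outcome the same within a domain". Further detail is referred to Additional file 4, which is not shown.

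**The concern.** The plan treats weighing at birth as something the programme can change. It then takes birth weight, which exists only where weighing took place, as a separate measure of effect. The birth-weight regression therefore runs on a subset whose make-up may depend on exposure.

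The setting makes this more than theoretical. About half of births are at home, and the programme aims to raise use of obstetric care. A woman who moves from home to facility birth may bring a baby into the weighed group who would otherwise have had no recorded weight. If such babies are lighter or heavier than those weighed anyway, mean birth weight moves with no change in any baby's health.

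At stake is how one outcome and one domain index are read. Neonatal health is the only domain whose items are all typed as health outcomes, and the Economic evaluation section accepts that power for mortality is lacking. A shift in this index could therefore well come from birth weight, the component open to the bias.

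**Working it through.** **1. Is the structure in the document?** Weighing and weight are both listed as outcomes in Table 4. That weight is missing for unweighed babies is not said in words; it follows from the retrospective survey source. With three equally weighted items, birth weight carries 1/3 of the index.

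**2. Does the model remove the selection?** Area fixed effects remove stable differences between areas. Quarter-year effects remove changes common to all areas, including a general rise in weighing. Neither removes a change in who is weighed that follows exposure within an area. The covariates help only as far as they explain the weight difference between newly weighed babies and the rest.

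**3. The plan's own figure.** The article gives no figure for birth weight or for the share weighed. The nearest is the design contrast for facility birth: 50% against 58%, 60 clusters per arm, 20 women per cluster, coefficient of variation k = 0.2, 80% power, 5% level (taken as two-sided).

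c = 1 + (1.960 + 0.842)² × [p0(1−p0)/m + p1(1−p1)/m + k²(p0² + p1²)] / (p1−p0)²

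= 1 + 7.849 × [0.0125 + 0.01218 + 0.02346] / 0.0064 = 60.03, against 60 stated. It reproduces. It is a detectable difference for facility birth, not an expected effect on weighing.

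**4. Illustrative shift with no true effect.** Let w0 be the share weighed without exposure and w1 the share with it. The newly weighed make up s = (w1−w0)/w1 of weighed exposed babies. If their mean weight differs by D from that of babies weighed anyway, the spurious shift is s × D. Carrying 50% to 58% over to weighing (assumption):

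- s = 0.08/0.58 = 0.138
- D = −0.1 kg: 0.138 × −0.1 = −0.014 kg
- D = −0.2 kg: 0.138 × −0.2 = −0.028 kg

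The sign reverses if the newly weighed babies are heavier.

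**5. Worst-case trimming bounds.** These assume normal weights and that exposure never causes a baby to go unweighed. The half-width is SD × φ(z)/(1−s), with z the (1−s) quantile. For s = 0.138, φ(z)/(1−s) = 0.256. At an assumed SD of 0.5 kg this is ±0.128 kg; at 0.4 and 0.6 kg it is ±0.102 and ±0.153 kg.

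**6. Range over the unknown share weighed** (D = −0.2 kg, SD = 0.5 kg, all assumed):

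| Share weighed | s | Shift | Bounds |
|---|---|---|---|
| 30% to 38% | 0.211 | −0.042 kg | ±0.18 kg |
| 50% to 58% | 0.138 | −0.028 kg | ±0.13 kg |
| 80% to 88% | 0.091 | −0.018 kg | ±0.09 kg |
| 50% to 54% | 0.074 | −0.015 kg | ±0.08 kg |

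**7. Scale.** With half of 60 × 20 = 1200 babies per arm weighed (600), SD 0.5 kg and clustering ignored, the endline detectable difference is 2.80 × 0.5 × √(2/600) = 0.08 kg. The shift of 0.014 to 0.028 kg is about one sixth to one third of that. In a standardised index it is 0.014/0.5/3 = 0.009 to 0.028/0.5/3 = 0.018 SD. The worst-case bounds of ±0.13 kg exceed 0.08 kg.

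**The case against.** The strongest reply is that Table 4 is a list of labels. Denominators, missing-value rules and sensitivity analyses belong in Additional file 4 or an analysis plan, so their absence is no fault. That is right, and no missing rule is held against the article. What stands is what the article itself fixes: an outcome conditional on another outcome, placed in an equally weighted index that is tested.

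Three other objections also hold.

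- **Only a differential change biases the estimate.** Weighing may rise in comparison areas too, and a common rise is absorbed by the quarter-year effects. A reader might infer that newly weighed babies appear only in exposed areas; nothing in the document says so.
- **Early deaths need not be lost.** A reader might infer that the index discards deaths because a baby who dies on day one may go unweighed. That happens only with a complete-case index. The article does not say the index is built that way; averaging available items, or averaging effects, drops no death.
- **The numbers are assumed and the illustrated shift is small.** Facility birth is a loose proxy for weighing: skilled personnel conducted 11%, 53% and 29% of home deliveries in the three districts, so weighing at home is possible. The trimming bounds are a worst case, not an expected bias.

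Finally, removing birth weight from the index may look like the natural remedy. It would leave two mortality items, one nested in the other, in a study not powered for mortality, and would alter a pre-specified grouping after the first survey round of January 2015. That case is not made out.

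**Conclusion.** The point holds in limited form. The birth-weight estimate, and its one-third share of the Neonatal health index, are open to selection bias if two conditions are met: exposure changes weighing differentially, and the newly weighed babies differ in weight after adjustment. The planned fixed effects and covariates do not remove it.

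Size and direction cannot be determined from the document, because the share weighed, the SD of birth weight and the weight difference are all unstated. On the illustrative assumptions the shift is about 14 to 28 g in either direction, which is small. The worst-case bounds of about ±0.13 kg mean that a birth-weight difference of detectable size could not by itself be read as a health effect.

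The primary outcome of facility birth is not touched, nor are the two mortality outcomes analysed separately. The mortality part of the index is affected only if the index is built on complete cases.

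**What to change.** - Label birth weight as an estimate among weighed babies. Report trimming bounds beside it, with the trimmed fraction taken from the already planned estimate for weighing at birth. If that estimate is zero, the bounds collapse to the point estimate.
- Keep the pre-specified Neonatal health index, and also report it without birth weight.
- State that the mortality items are computed on all live births, so that no baby is dropped, in the index or elsewhere, for a missing birth weight.

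All of this uses data already being collected. The cost is some wording, one extra sensitivity analysis, and a birth-weight result that may have to be given as a range.
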